## Abstract

**Background:**

Anhedonia and other deficits in reward- and motivation-related processing in psychiatric patients, including patients with major depressive disorder (MDD), represent a high unmet medical need. Neurobiologically, these deficits in MDD patients are mainly associated with low dopamine function in a frontostriatal network. In this study, alterations in brain activation changes during reward processing and at rest in MDD patients compared with healthy subjects are explored and the effects of a single low dose of the dopamine D2 receptor antagonist amisulpride are investigated.

**Methods:**

This is a randomized, controlled, double-blind, single-dose, single-center parallel-group clinical trial to assess the effects of a single dose of amisulpride (100 mg) on blood-oxygenation-level-dependent (BOLD) responses during reward- and motivation-related processing in healthy subjects (*n* = 60) and MDD patients (*n* = 60). Using functional magnetic resonance imaging (fMRI), BOLD responses are assessed during the monetary incentive delay (MID) task (primary outcome). Exploratory outcomes include BOLD responses and behavioral measures during the MID task, instrumental learning task, effort-based decision-making task, social incentive delay task, and probabilistic reward task as well as changes in resting state functional connectivity and cerebral blood flow.

**Discussion:**

This study broadly covers all aspects of reward- and motivation-related processing as categorized by the National Institute of Mental Health Research Domain Criteria and is thereby an important step towards precision psychiatry. Results regarding the immediate effects of a dopaminergic drug on deficits in reward- and motivation-related processing not only have the potential to significantly broaden our understanding of underlying neurobiological processes but might eventually also pave the way for new treatment options.

**Trial registration:**

ClinicalTrials.gov NCT05347199. April 12, 2022.

**Supplementary Information:**

The online version contains supplementary material available at 10.1186/s13063-023-07788-x.

## Introduction

### Background and rationale

Major depressive disorder (MDD) is a leading cause of disability with a worldwide prevalence of over 264 million [1, 2] and represents a high burden for affected individuals, their families, and the society as it comes along with high treatment costs and long periods of hospitalization [2, 3]. Core symptoms are depressed mood and the inability to experience pleasure (anhedonia) [4]. First-line antidepressant treatment approaches often do not relieve anhedonic symptoms [5–7], which constitute a key predictor for poor treatment response [8, 9]. Yet, no dedicated treatment options for anhedonia are available for patients.

One reason why antidepressants have limited efficacy in treating anhedonia is that other than as indicated in the diagnostic criteria, anhedonia does not only encompass reduced capability to feel pleasure. It rather comprises multiple processes and stages related to reward and motivation with different neurobiological correlates involved. A research framework for the investigation of these processes is provided by the National Institute of Mental Health Research Domain Criteria (RDoC) [10], where they are conceptualized in the domain *Positive Valence Systems* comprising the constructs Reward Responsiveness, Reward Learning, and Reward Valuation. The RDoC also provides information about the neurobiological underpinnings of these processes and recommendations regarding tasks and self-report tools for their investigation.

The neurobiological substrates include ventromedial prefrontal/orbitofrontal cortex (vmPFC/OFC), anterior cingulate cortex (ACC), striatum, and ventral tegmental area (VTA) [11, 12] and require dopaminergic signaling [13, 14]. The monetary incentive delay (MID) task is a robust and well-validated task to investigate neural correlates of Reward Responsiveness in the ventral striatum, ACC, and salience network during reward anticipation and reward outcome [15–17]. Commonly used tasks to investigate Reward Learning and Reward Valuation are instrumental and reversal learning tasks, probabilistic reward task, and effort-based valuation tasks [18–21].

Most human studies investigated reward- and motivation-related processing in human experimental settings using monetary reward. However, as other entities like food or social interaction are intrinsically rewarding and therefore comparable according to preclinical research, variations of classical reward tasks also include social reward or food reward [22, 23].

Compared to healthy volunteers (HV), blunted activation in frontostriatal brain regions and poor behavioral responses during reward- and motivation-related decision-making were observed in MDD [24]. Several attempts have been made to investigate the effects of pharmacological intervention on reward- and motivation-related deficits in MDD [25–29]. However, mixed effects have been reported in this context and neurobiological mechanisms underlying deficits in reward- and motivation-related processing are still unclear.

A promising option to investigate treatment effects on reward- and motivation-related deficits is to specifically target dopaminergic neurotransmission in frontostriatal brain regions by using pharmacological interventions that are specific for and have high affinity to dopamine receptors such as amisulpride [25, 29]. Amisulpride’s pharmacological efficacy relates to its high mesolimbic affinity and its properties as a selective dopamine D2/D3 receptor antagonist at the postsynapses at high doses (400–1200 mg per day) [30, 31]. At a low dose (50–300 mg per day), amisulpride has a higher affinity to block presynaptic autoreceptors and thereby increases dopaminergic signaling at the synapse [31].

Amisulpride reduced striatal activation and worsened behavioral performance during an instrumental learning task in HV at a high single dose (400 mg) [32], while at a single lower dose (200 mg) it improved reward learning and enhanced striatal activation during the task [33]. During reward anticipation as assessed using the MID task; however, no effect of a single low dose (200 mg) of amisulpride was observed, which could possibly be due to ceiling effects in healthy subjects [34]. In MDD, associated with dopamine deficiency, single low-dose amisulpride (50 mg) enhanced striatal activations and enhanced connectivity between the ventral striatum and midcingulate cortex during the MID task compared to HV, but did not impact impaired reward learning in MDD patients [29, 35]. The effects of amisulpride on reward valuation in MDD have not been investigated yet.

The aim of this study is to selectively manipulate striatal dopamine signaling using amisulpride during the processing of different reward- and motivation-related tasks. To our knowledge, no functional magnetic resonance imaging (fMRI) study has yet tested in both HV and MDD patients if transiently enhancing dopamine signaling by using a single low dose of amisulpride impacts (1) processing of different reward- and motivation-related tasks that cover all three RDoC constructs of Positive Valence Systems; (2) processing of different reward types (monetary reward and social reward); and (3) functional connectivity at rest and cerebral blood flow.

## Methods

### Study design

This single-center, double-blind, placebo-controlled, randomized, single-dose, parallel-group study is designed to investigate the effects of a single dose of amisulpride on functional brain changes during reward- and motivation-related processing and at rest. The study is conducted by the Charité Research Organisation, a contract research organization and subsidiary of the Charité – Universitätsmedizin Berlin. A total of 120 participants will be recruited. Measurement of functional brain changes is performed after a single dose of amisulpride or placebo in HV and patients with MDD.

It is hypothesized that functional brain changes previously linked to reward- and motivation-related processing require dopaminergic signaling and are diminished in MDD compared to HV. In MDD, but not in HV, the administration of a single low dose (100 mg) of amisulpride should increase brain activation associated with reward- and motivation-related processing.

MDD patients (*n* = 60) and HV (*n* = 60) are randomly allocated in a 1:1 ratio to the two treatment arms (MDD/amisulpride *n* = 30, MDD/placebo *n* = 30, HV/amisulpride *n* = 30, HV/placebo *n* = 30). The effects of a single dose of amisulpride (100 mg) on functional brain changes are assessed during reward- and motivation-related processing and at rest.

The study is composed of four outpatient visits (see Table 1): screening, baseline, and two scanning sessions (visit 3 and visit 4). During screening, subjects provide written informed consent, and all subjects must satisfy all inclusion and exclusion criteria (see eligibility criteria). Further assessments during screening comprise demographics and medical history, physical examination, height and weight, urine pregnancy test, follicle-stimulation hormone (FSH) test, urine drug screen, alcohol breath test, vital signs, electrocardiography (ECG), adverse events, concomitant medication, hematology, chemistry, and coagulation, severe acute respiratory syndrome coronavirus type 2 (SARS-CoV-2) test, as well as the Structured Clinical Interview for DSM-5 (SCID-5) [36], the Montgomery-Åsberg Depression Rating Scale (MADRS) [37], and the Columbia Suicide Severity Rating Scale (C-SSRS) [38]. During the baseline visit, examinations comprise inclusion and exclusion criteria, urine pregnancy test, urine drug screen, alcohol breath test, concomitant medication, and hematology, chemistry, and coagulation. All eligible subjects undergo MRI scanning at visit 3 and visit 4 which are eight days apart from each other. On visits 3 and 4, before the administration of amisulpride or matching placebo, inclusion and exclusion criteria and, again, urine pregnancy test, urine drug screen, alcohol breath test, vital signs, 12-lead ECG, and a SARS-CoV-2 test are assessed. Hematology, Chemistry, and coagulation are examined before drug administration on visit 3 and after drug administration on visit 4. Adverse events and concomitant medication are assessed throughout visits 3 and 4. In the time window between predose and the MRI assessments, all subjects complete several psychopathology questionnaires (Beck Depression Inventory (BDI) [39], Snaith-Hamilton-Pleasure-Scale (SHAPS) [40], Dimensional Anhedonia Rating Scale (DARS) [41], and Leuven Affect and Pleasure Scale (LAPS) [42]) to probe depressive symptomatology and anhedonia.

**Table 1 Tab1:** Schedule of assessments

Event and comment	SCR	Baseline	Treatment day							Treatment day						
Visit number	1	2	3							4						
Study day^a^	− 28 to − 4	− 3 to − 1	1 2							8 ± 2						
Hours post amisulpride or placebo			Predose	0:00	1:00	1:15	3:30	4:30	4:45	Predose	0:00	1:00	1:15	3:30	4:30	4:45
Written informed consent	**x**															
Inclusion/exclusion criteria	**x**	**x**	**x**							**x**						
Demographics and medical history	**x**															
Physical examination	**x**															**x**
Weight/height	**x**															
Urine pregnancy test^b^	**x**	**x**	**x**							**x**						
FSH test	**x**															
Urine drug screen	**x**	**x**	**x**							**x**						
Alcohol breath test	**x**	**x**	**x**							**x**						
Vital signs^c^	**x**		**x**							**x**						
12-lead ECG	**x**		**x**													**x**
Adverse events	**x**	**x**	**x**							**x**						
Concomitant medication	**x**	**x**	**x**							**x**						
Hematology, chemistry, coagulation^d^	**x**		**x**													**x**
COVID-19 test^e^	**x**	**x**	**x**							**x**						
Randomization		**x**														
Intake of amisulpride or placebo				**x**							**x**					
Breakfast^f^						**x**							**x**			
PK blood amisulpride^g^			**x**		**x**		**x**	**x**		**x**		**x**		**x**	**x**	
Headache severity NRS							**x**	**x**						**x**	**x**	
SCID-5-CV^h^	**x**															
MADRS^i^	**x**															
Columbia Suicide Severity Rating Scale^j^	**x**															
Questionnaires Psychopathology Set^k^				**x**	x	x					**x**	x	x			
MR Scanner trial activity Set 1^l^^((1), (2), (3), (4))^							**x**									
MR Scanner trial activity Set 2^l^^((1), (5), (6))^														**x**		
Behavioral paradigm^m^									**x**							

^a^There is a treatment-free interval of 7 ± 2 days between visits 3 and 4

^b^Urine pregnancy test (if urine test positive, blood test to be done)

^c^Vital signs: pulse rate, systolic and diastolic blood pressure (BP), and body temperature in the ear

^d^Hematology: leukocytes, granulocytes, neutrophils, eosinophils, basophiles, lymphocytes, monocytes, erythrocytes, thrombocytes, hematocrit, hemoglobin; chemistry: sodium, potassium, calcium, magnesium, total protein, albumin, glucose, creatinine, urea, bilirubin, ASAT, ALT, GGT, LDH, AP, CRP; Coagulation: aPTT, INR; * no coagulation at Visit 3 and 4

^e^Prior to Randomization

^f^Time window: 1:15 ± 15 min after amisulpride intake

^g^Time windows: 1:00 + 5 min, 3:30 + 30 min, 4:30 + 30 min

^h^SCID-5-CV (DSM-5, Beesdo-Baum, Zaudig, and Wittchen, 2019); * within 14 days prior to visit 3

^i^MADRS (Montgomery-Åsberg Depression Rating Scale, Montgomery and Åsberg, 1979); * within 14 days prior to visit 3

^g^Columbia Suicide Severity Rating Scale (C-SSRS, Posner et al., 2011); * within 14 days prior to visit 3

^k^Questionnaires Set: Beck Depression Inventory (BDI; Beck et al., 1961); Snaith-Hamilton-Pleasure-Scale (SHAPS; Snaith et al., 1995); Dimensional Anhedonia Rating Scale (DARS; Rizvi et al., 2015); Leuven Affect and Pleasure Scale (LAPS; Demyttenaere et al., 2019)

^l^MRI: (1) high-resolution anatomical MRI scan; (2) resting-state functional magnetic resonance imaging (rsfMRI); (3) MID task; (4): instrumental learning fMRI task; (5) SID task; (6) effort-based decision-making fMRI task; (7) arterial spin labeling (ASL)

^m^Time window for probabilistic reward task: ± 30 min

Treatment with amisulpride or matching placebo occurs 3.5 to 4 h before the start of each scanning session. 1 to 1.5 h after the intake of amisulpride or matching placebo, subjects are served a standardized breakfast. Multimodal MR brain imaging (high-resolution anatomical MRI scan, resting state fMRI, task-based fMRI, arterial spin labeling (ASL)) is performed on two separate days where subjects first undergo an anatomical scan. On visit 3, the anatomical scan is followed by a resting state scan, two fMRI tasks (MID task [15] task and instrumental learning task (ILT) [21], an ASL sequence, and the probabilistic reward task (PRT) [18] as a pure behavioral measure of reward learning which is performed outside the scanner. The MID task is the first task presented inside the scanner to prevent it from being affected by fatigue as it is the primary outcome. On visit 4, the anatomical scan is followed by two different fMRI tasks (social incentive delay task (SID) [43] and effort-based decision-making (EBDM) task [20]. The SID task is presented before the EBDM task as physical effort is required to perform the assessments. Headache severity is measured using a numeric ranking scale to control for possible confounding of the MRI assessments by headache. MRI assessments are conducted at two visits to not exceed a scanning time of 60 min each. A timeline for substance administration and MR protocol for each experimental group at visit 3 and visit 4 can be found in Fig. 1. Time of treatment is standardized across subjects.

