**Fig. 1 Fig1:**
[figure not shown]
Timeline for substance administration and MRI protocol for each experimental group at visit 3 and visit 4

At visit 3 and visit 4, blood samples are taken 30 min pre-dose, and 1 h, 3.5 to 4 h, and 4.5 to 5 h after oral drug administration to assess the pharmacokinetics of amisulpride. On visit 4, after the MRI measurements, a physical examination, as well as 12-lead ECG, hematology, chemistry, and coagulation, is performed. A description and a detailed schedule of assessments can be found in Table 1, including questionnaires, laboratory tests, MRI, and the behavioral paradigm.

All assessments are performed by trained professionals in a standardized manner. In order to ensure high-quality standards of the assessments, a common digital manual as well as quality monitoring procedures are implemented (see the “Data management and monitoring” section).

This study was designed by the MSB Medical School Berlin (LC, DW, MSM, SG) and Boehringer Ingelheim Pharma GmbH & Co. KG (MP, GL, SDS, AW). The Charité Research Organisation (CK, RH), a contract research organization and subsidiary of the Charité – Universitätsmedizin Berlin, is responsible for the implementation and, together with the MSB Medical School Berlin, conduction of the trial. SG (MSB Medical School Berlin) is the grant holder and sponsor. SBGneuro Ltd (CB) is responsible for the statistical analysis plan including power analysis. For the interpretation of the data, the responsibility lies with the researchers of the MSB Medical School Berlin. Study organization, recruitment of participants, and monitoring are performed by the Charité Research Organisation (CK, RH). This study is conducted in compliance with Good Clinical Practices (ICH-GCP) and the Declaration of Helsinki. A clinical trial registration is available on ClinicalTrials.gov (NCT number: NCT05347199). The trial is funded by Boehringer Ingelheim Pharma GmbH & Co. KG and approved by the respective local ethics committee (Landesamt für Gesundheit und Soziales, Geschäftsstelle der Ethik-Kommission des Landes Berlin, Berlin, Germany; reference number: 22/029 – IV E 11) and the Bundesinstitut für Arzneimittel und Medizinprodukte, Bonn, Germany.

The reporting of this study protocol was performed according to the Standard Protocol Items Recommendations for Interventional trials (SPIRIT; [44]).

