### Relevant concomitant care

During the screening period, prior and concomitant medications are recorded and reviewed throughout the study until visit 4. In particular, prescribed medication or psychotherapy as mentioned above are not permitted as concomitant treatments. Subjects who have taken prescription or non-prescription medication may still be entered into the study, if, in the opinion of the investigator, the medication does not interfere with the study procedures or compromise safety. Amisulpride will not be used in combination with medications which, e.g., could induce torsade de pointes (such as class Ia and class III antiarrhythmic agents), as well as other medications as indicated in the label of amisulpride.

If concomitant drugs are administered, these are recorded in the subjects’ file and eCRF. Permitted concomitant treatments are not to be changed during the course of this study.

Moreover, the following criteria concerning diet and lifestyle result in the withdrawal of the study subject:Consumption of large amounts of caffeinated drinks (more than 8 cups of standard caffeinated drinks (tea, instant coffee) or 6 cups of stronger coffee or other drinks containing methylxanthines such as Coca-Cola or Red Bull per dayConsumption of caffeinated drinks 2 h prior to the start of the fMRI scanSmoking/nicotine consumption 2 h prior to the start of the fMRI scanConsumption of food containing poppy seeds within 24 h prior to visits 3 and 4Consumption of alcohol within 24 h prior to visits 3 and 4.

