The clinical study protocol was first submitted on February 11, 2022, to the competent authorities. The independent ethics committee approved the protocol on March 3, 2022, with conditions. One condition was that it should be guaranteed that MDD patients enrolled in the trial were diagnosed and treated by staff experienced and certified for the treatment of major depressive disorder (psychiatrists, psychologists). The protocol amendment includes that subjects treated with antidepressants would not be included in the study and that subjects who received antidepressant treatment prior to study enrollment should not interrupt or wash out treatment for study purposes. Furthermore, it was specifically mentioned that no subjects with a QT prolongation at screening ECG should be enrolled in the study. An additional ECG assessment was included predose at Visit 4 for safety reasons. In addition, in the amended clinical study protocol clarifications to the study endpoints, study objectives, contraindicated concomitant medications, maximum number of subject replacements, treatment randomization, replacement in the event of headache, sample size, statistical analysis, and minor grammatical, formatting, or spelling corrections were made. After receiving final approval from the independent ethics committee and the Bundesinstitut für Arzneimittel und Medizinprodukte, recruitment was started.

Screening procedures of the first healthy volunteers revealed that the lower limits for systolic and diastolic blood pressure (100 mmHg and 65 mmHg) needed to fulfill eligibility criteria were defined too narrowly. More than 50% of all screened healthy volunteers could not pass the screening visit successfully. With an amendment of the clinical study protocol, the lower limits of blood pressure were reduced to 50 mmHg for diastolic blood pressure and to 90 mmHg for systolic blood pressure. Since a reflex tachycardia might occur in response to low blood pressure, the upper limit of the pulse rate was increased to 100 bpm (instead of 90 bpm) for inclusion. With the implementation of these new limits (after approval by the independent ethics committee and the Bundesinstitut für Arzneimittel und Medizinprodukte) the screening process was optimized resulting in a reduced screen failure rate.

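### Table 1 leaves out the visit 4 predose ECG that the text requires and says was added for safety

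*Protocol article*

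**What the plan says.** The running text of the protocol article places ECGs at four time points.

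- **Screening.** The Study design section lists "alcohol breath test, vital signs, electrocardiography (ECG), adverse events" among the screening assessments.
- **Before dosing at visits 3 and 4.** The same section opens its predose list with "On visits 3 and 4, before the administration of amisulpride or matching placebo" and ends it with "alcohol breath test, vital signs, 12-lead ECG, and a SARS-CoV-2 test are assessed". This gives one ECG at each of the two visits.
- **After scanning at visit 4.** The text following Fig. 1 states: "On visit 4, after the MRI measurements, a physical examination, as well as 12-lead ECG, hematology, chemistry, and coagulation, is performed".

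The Discussion, describing the amendments, confirms the visit 4 predose item: "An additional ECG assessment was included predose at Visit 4 for safety reasons". It also says that "no subjects with a QT prolongation at screening ECG should be enrolled in the study".

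Table 1, to which the Study design section sends the reader for the detailed schedule, marks the 12-lead ECG at screening, visit 3 predose and visit 4 at 4:45 h. The visit 4 predose cell is empty.

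**The concern.** Text and table are both current and disagree on a safety assessment. The Eligibility criteria exclude participants with QT prolongation. The Relevant concomitant care section keeps amisulpride apart from drugs that "could induce torsade de pointes". Table 1 itself has the inclusion and exclusion criteria rechecked before the second dose.

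Neither text nor table schedules an ECG after dosing at visit 3. The visit 4 predose recording is therefore the only one between the two doses. If staff worked from the table as printed, they would recheck eligibility before re-exposure without a new ECG, and the check that the Discussion says was added for safety would be the one dropped. The entry check at screening and the visit 3 predose ECG would remain.

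**Working it through.** This is a count and a comparison; no statistical formula applies.

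**1. Table 1 as printed.** The table has 16 time columns: screening (1), baseline (2), visit 3 from predose to 4:45 h (3 to 9) and visit 4 from predose to 4:45 h (10 to 16). The relevant rows are marked as follows.

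| Row | Marked columns |
|---|---|
| 12-lead ECG | 1, 3, 16 |
| Vital signs | 1, 3, 10 |
| Inclusion/exclusion criteria | 1, 2, 3, 10 |
| Physical examination | 1, 16 |
| Hematology, chemistry, coagulation | 1, 3, 16 |

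The ECG row has all its fields (the row label plus 16 time cells), so no cell was lost or shifted when the text was extracted. ECG count in the table: 3.

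**2. The text.** 1 (screening) + 1 (visit 3 predose) + 1 (visit 4 predose) + 1 (visit 4 after MRI) = 4. The article never writes the number four; it is the sum of the time points it names.

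**3. Where they differ.** 4 − 3 = 1, and the missing mark is column 10, visit 4 predose.

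**4. Could the 4:45 h mark be the predose ECG in the wrong place?** No. The text puts the post-MRI ECG of visit 4 together with the physical examination and the laboratory tests, and all three rows are marked in column 16. That mark is where it belongs.

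**5. Is the predose list otherwise carried into the table?** Yes. The list for visits 3 and 4 has seven items: criteria, pregnancy test, drug screen, alcohol test, vital signs, ECG and SARS-CoV-2 test. Six are marked at visit 4 predose. Only the ECG is not.

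**6. Gap under Table 1.** Footnote a gives 7 ± 2 days between visits 3 and 4. Taken from dose to dose, that is 7 − 2 = 5 to 7 + 2 = 9 days. The next ECG after the first dose is at 4:45 h after the second dose, hence 5 to 9 days plus 4:45 h. The Study design text gives eight days between the visits, which lies within this range. Under the text, one ECG falls between the two doses; under the table, none does.

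**7. After the correction.** With column 10 marked, the table shows 4 ECGs and agrees with the text.

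**The case against.** The strongest case is that this is one empty cell whose intended content the article makes plain. The text requires the ECG in the Study design section and mentions it again in the Discussion, so a reader of both knows what is meant. The harm depends on the site working from the printed table, while the full protocol is a separate document and the article describes a common digital manual, training, monitoring and close oversight of visits. The Discussion also states that the interval gives complete washout before the second dose. On that footing the visit 4 predose ECG is an off-drug recheck and does not measure the first dose's QT effect. The Discussion ties the QT exclusion to the screening ECG, the dose is low, and marking the eligibility criteria at visit 4 predose might prompt an ECG indirectly.

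Most of this stands as a limit on weight. The intention is clear, no missed ECG is shown, and the washout statement narrows the purpose of the recording to finding new or unnoticed QT risk before re-exposure. It does not remove the mismatch. Table 1 is the place the article names for the detailed schedule, and it omits the one added check. Nor is the conflict a difference between an amendment summary and current text: it lies between the current Study design text and the current table, and the Discussion agrees with the text.

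**Conclusion.** The concern holds. Table 1 shows three ECGs per participant where the text names four, and the missing one is the visit 4 predose recording. If the table were followed, the second dose would be given with no ECG since before the first, and the next would come 5 to 9 days plus 4:45 h after the first dose. What would be lost is the check before re-exposure; the checks at entry would remain.

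The practical consequence assumes that the site's working schedule repeats the table, which the article does not show. Sample size, alpha and the primary analysis are not affected. The point merits correction because it concerns a safety check and costs almost nothing to put right.

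**What to change.** Add a mark at visit 4 predose in the 12-lead ECG row of Table 1 and keep the mark at 4:45 h. Confirm that the site's working schedule includes the predose ECG; recruitment was described as ongoing under Trial status, so the check could still matter. The cost is one mark and one look at the schedule.

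Three other slips can be corrected in the same pass. They are editorial and have no bearing on the second dose.

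- Footnote d rules out coagulation tests at visits 3 and 4, while the Study design text includes them at both.
- The Study design text lists laboratory tests at baseline, but Table 1 has no baseline mark in that row.
- ASL, item (7) in footnote l, is in neither scanner set; the text places it at visit 3, so it belongs in Set 1.
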